**Outcome measures**

Primary outcome measures include laboratory assessments of nicotine reinforcement and smoking cue reactivity. The measure of nicotine reinforcement is the percentage of nicotine cigarette puffs chosen during the forced-choice task. Measures of cue reactivity include tobacco craving, mood, and autonomic responsivity.

The secondary outcome measure is days of smoking abstinence during the quit-attempt weeks. Abstinence is assessed by self-reports of no smoking and by breath carbon monoxide < 5 ppm. Other assessments of abstinence include self-reported tobacco craving and withdrawal.

Sociodemographic and baseline measures (e.g., smoking history, level of nicotine dependence, number of cigarettes smoked per day, tobacco craving, mood, smoking motivations) will be used to characterize the sample and explore as mediators of primary and secondary outcomes.

**Statistical Analysis**

Standard techniques will be used to examine the distributional properties of the data (means, standard deviations, medians, skewness, kertosis) in order to verify that all assumptions are met for subsequent analyses. The data will be examined for univariate and multivariate outliers. For all analyses, results are considered significant at *p*<.05.

Aim 1:Investigate the effect of gemfibrozil on laboratory measures of nicotine reinforcement and cue-elicited craving

The percentage of puffs chosen from Nic cigarettes in the forced-choice sessions will be analyzed using mixed-model analysis of variance (ANOVA) with drug condition (placebo, gemfibrozil) as within-subject factors and order of exposure of drug condition and order of exposure of cigarette type (Nic, Denic) as between-subject factors. For cue-reactivity sessions, self-report and physiological measures will be analyzed by mixed-model ANOVA, with drug condition (placebo, gemfibrozil), cue type (smoking, nonsmoking) and time post-cue (0, 15 minutes) as within-subject factors and order of exposure of drug condition and cue type as between-subject factors. For measures showing significant main effects or interactions, post hoc comparisons between means will be conducted. Supplemental analyses may be conducted using bivariate analyses to identify relationships to participant-level variables (e.g., socioeconomic factors, mood). Variables identified will be used as covariates if they are believed to be suppressor variables or entered into stepwise regressions to better characterize the participants for whom gemfibrozil has the greatest effect on laboratory measures.

Aim 2: Screen for the ability of gemfibrozil to aid smoking abstinence during a brief quit attempt

Data from the quit-attempt will be analyzed using mixed-model ANOVA with drug condition (placebo, gemfibrozil) as a within-subject factor and order of exposure of drug condition as a between-subject factor. Post hoc comparisons between means will be conducted on significant overall effects. Supplemental analyses may be conducted using bivariate analyses to identify relationships to participant-level variables (e.g., socioeconomic factors, mood). Variables identified will be used as covariates if they are believed to be suppressor variables or entered into stepwise regressions to better characterize the participants for whom gemfibrozil facilitates smoking abstinence.

Aim 3: Examine the validity of using laboratory measures of tobacco dependence to predict smoking abstinence and possible gemfibrozil-related increases in smoking abstinence

Bivariate correlational analyses will be used to determine the predictive association between laboratory measures of nicotine reinforcement and cue reactivity and tobacco abstinence during the quit-attempt. Two multivariate stepwise regressions will then be constructed to determine multivariate predictors of abstinence days and gemfibrozil-related change in abstinence days. At step one, demographic variables will be entered. At step two, smoking-related characteristics that are significantly associated with abstinence will be entered. Finally, at step three, measures of laboratory performance in both forced-choice and cue-reactivity that were significant in bivariate analyses will be entered to determine their multivariate predictive validity for smoking abstinence.

Power Analysis

Based on the preclinical data, we expect that gemfibrozil will decrease cue-reactivity, the number of puffs taken on the nic cigarette and increase abstinence. The preclinical data suggest that observed effect size of those effects will be around 0.5. However, those effect sizes may be lower in human subjects. As we have currently no data on human subjects, we decided to power the study to be able to detect a smaller effect size. Taken into account the variance of the behavioral responses based on the previous human laboratory studies (McKee et al., 2011), with 40 subjects, we will have sufficient power (>80%) at an alpha level of 0.05 to detect differences between conditions (gemfibrozil vs placebo) as small. This study will provide the necessary data to determine the effect size of gemfibrozil on these measures and preliminary evidence on the potential utility of gemfibrozil as a smoking cessation pharmacotherapy. Based on the results obtained, we can submit further grants to conduct a clinical trial to investigate the efficacy of gemfibrozil as a smoking cessation medication.

Missing, unused and spurious data:

Missing data will be dealt with according to statistical principles for filling in missing cells. In the event that large amounts of data are missing due to, for example, participant noncompliance with study procedures, the data will be analysed according to the primary goals of the study and the objectives of this study. Statistical procedures that deviate from the protocol will be reported and justified in a protocol deviation log.

The data from all eligible subjects will be included in the data analysis

Accrual Number

There are several factors that could adversely affect accrual and completion of this study: a) participants may quit during the first medication phase; b) some participants might experience intolerable side effects of gemfibrozil; and c) some participants might not be compliant with taking medication. Given these factors, we anticipate up to 50% attrition. Drop-outs will be replaced.

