[figure not shown]

[figure not shown]

**Fig. 3.**Change from pre- to post- exposure of smoking and neutral cues in visual analog ratings of cigarette craving and urge to smoke (n = 30). From NIDA Study 456.

Brief Assessment of Smoking Abstinence

Up to now, the only valid approach to test the efficacy of a new medication to treat tobacco dependence has been a clinical trial. Such trials typically require large numbers of participants, take months or years to complete, and are expensive. As a result, they are not practical as an initial test of a medication’s efficacy. Recently, Perkins and colleagues (Perkins et al. 2006, 2008, 2010a) developed a new methodology to determine the efficacy of potential medications to treat tobacco dependence. In addition to the impracticality of clinical trials mentioned above, the need for a new screening methodology arose from the realization that current short-term studies that assess the ability of medications to relieve abstinence-induced withdrawal or to decrease the reinforcing effects of smoking do not reliably predict treatment efficacy (Perkins et al. 2006). For example, although nicotine replacement therapy (NRT, patch or gum), bupropion (Zyban®), and varenicline (Champix®) are FDA and Health Canada-approved medications with known efficacy for smoking cessation (Fiore et al. 2008), they have not reliably reduced nicotine withdrawal symptoms or ad libitum smoking in numerous short-term laboratory studies (Perkins et al. 2006, 2010b).

One possible reason that short-term medication studies have not predicted clinical efficacy is that most studies were conducted with smokers not interested in quitting. This lack of motivation to quit smoking would be exclusionary for a clinical trial and thus likely confounded the results of many short-term screening studies. These studies also typically exposed participants to drug for brief durations and assessed withdrawal or craving rather than tobacco abstinence. Thus, Perkins et al. (2006) proposed the following screening methodology: (a) recruitment of smokers planning to quit in the near future, (b) administration of drug for an extended duration, and (c) assessment of tobacco abstinence in participants’ natural environments. Such studies would also retain the advantages of the typical screening study, including brief duration and use of a within-subjects design, which allows increased statistical power with a relatively small sample size.

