**Study Aims and Hypotheses**

The study aims are:

1. to investigate the effect of gemfibrozil on laboratory measures of nicotine reinforcement and cue-elicited craving
2. to screen for the ability of gemfibrozil to aid smoking abstinence during a brief quit attempt
3. to examine the validity of using laboratory measures of tobacco dependence to predict smoking abstinence and possible gemfibrozil-related increases in smoking abstinence.

Based on preclinical data discussed above, we hypothesize that:

1. Gemfibrozil will result in diminished nicotine reinforcement compared with placebo. This will be evidenced by participants choosing a lower percentage of puffs from nicotine cigarettes (vs. denic cigarettes) when taking gemfibrozil compared with placebo.
2. Gemfibrozil will result in an attenuated response to smoking cues. This will be evidenced by diminished autonomic responses (e.g., heart rate) and self-report responses (e.g., craving) to smoking cues (vs. neutral cues) when taking gemfibrozil compared with placebo.
3. Gemfibrozil will increase smoking abstinence. This will be evidenced by a greater number of days abstinent when taking gemfibrozil compared with placebo.
4. Laboratory measures of smoking will prove valid in predicting abstinence. This will be evidenced by percentage of puffs from nicotine cigarettes chosen in the forced-choice task and response to smoking cues being negatively associated with number of days abstinent.
5. Likewise, the difference in laboratory measures, when comparing the gemfibrozil and placebo conditions, will predict the difference in abstinence days, when comparing the gemfibrozil and placebo conditions.

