a) *Cue-reactivity.* The cue-reactivity session occurs after one week of medication. There are two cue conditions tested in the session, one with smoking cues and the other with nonsmoking cues. Order of the two conditions will be counterbalanced across participants. Participants start by completing baseline self-report measures (TCQ-SF, Mood Form, VAS, MNWS). Cue conditions are then begun. Each cue condition begins with participants seated in a comfortable chair and smoking 4 puffs from their preferred-brand cigarette. Participants are then presented with a tray containing an opaque cover. In the smoking-cue condition, a pack of the participant’s preferred brand of cigarettes, a lighter, and an ashtray are under the tray cover. In the nonsmoking-cue condition, a pack of unsharpened pencils, a pencil sharpener, and a small notepad are under the cover. Participants are then connected to physiological recording devices to measure skin conductance, skin temperature, heart rate and blood pressure. This is followed by 10 minutes of audio-instructed progressive relaxation. Participants are then given the Mood form, TCQ-SF and VAS. After resting for 5 minutes, baseline physiological measures are recorded for 5 minutes. When instructed, the participant lifts the cover on the tray. In the smoking-cue condition, participants take one cigarette out of the pack, light it without puffing, hold it for 1 minute, extinguish the cigarette, and replace the cover on the tray. In the nonsmoking-cue condition, participants take one pencil out of the pack, sharpen it, hold it for 1 minute as if to write on the notepad, and then replace the cover. Participants complete the TCQ-SF, Mood Form, and VAS immediately and 15 minutes after cue presentation; physiological measures are recorded continuously.

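### The cue-reactivity model leaves out the pre-cue measurements and does not name drug × cue type as the test of Hypothesis 2, which costs precision and lets a drug main effect be read as reduced reactivity

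*Protocol*

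**What the plan says.** The protocol's description of the cue-reactivity session (Study Design and Methods) sets out the same sequence for the smoking-cue and the nonsmoking-cue condition. After four puffs and a relaxation period, and before the tray is uncovered, "Participants are then given the Mood form, TCQ-SF and VAS". Then "After resting for 5 minutes, baseline physiological measures are recorded for 5 minutes". After the cue, "Participants complete the TCQ-SF, Mood Form, and VAS immediately and 15 minutes after cue presentation; physiological measures are recorded continuously". With two cue conditions and two drug phases, each completer has four sets of pre-cue and post-cue data. Cue order is counterbalanced.

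The Statistical Analysis section, Aim 1, says: "For cue-reactivity sessions, self-report and physiological measures will be analyzed by mixed-model ANOVA". The factors are drug condition, then "cue type (smoking, nonsmoking) and time post-cue (0, 15 minutes) as within-subject factors", with order of drug and order of cue type between subjects. Post hoc comparisons follow whichever main effects or interactions reach significance.

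Hypothesis 2 (Study Aims and Hypotheses) reads "Gemfibrozil will result in an attenuated response to smoking cues" and defines that response as smoking versus neutral cues, compared between gemfibrozil and placebo. The protocol's own supporting data in the Introduction (Fig. 3) are shown as "Change from pre- to post- exposure of smoking and neutral cues in visual analog ratings of cigarette craving and urge to smoke". Outcome Measures lists cue reactivity among the primary outcomes.

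**The concern.** There are two weaknesses.

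1. **Unused data.** The stated time factor has post-cue levels only, and no other term brings in the pre-cue values. People differ in where they start before each cue, and some will still carry craving from the first cue when the second begins. That variation stays in the error although it was measured.
2. **Unnamed test.** The hypothesis is about one interaction, but the analysis text treats all effects alike. If gemfibrozil lowered craving or heart rate generally, with no change in the response to cues, post-cue scores would be lower under both cue types and the drug main effect would be significant. Reading that as attenuated cue reactivity would be a wrong conclusion on a primary outcome, and the Power Analysis says the results may support further grants.

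**Working it through.** **Inputs from the protocol.** Post-cue times of 0 and 15 minutes; two cue types; two drug phases; 40 subjects; alpha 0.05 (Power Analysis); an approved ceiling of 30 completers (Human Subjects Protections).

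**Assumptions, not in the documents.** r, the pre-post correlation of the within-person drug × cue contrast; a standardised contrast effect of 0.4; two-sided testing; equal pre-cue and post-cue variances.

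**The plan's own figure.** The protocol claims more than 80% power with 40 subjects but gives no number for the small effect it targets, so the claim can be neither reproduced nor refuted. For a within-subject contrast (noncentral t, 39 degrees of freedom), power is 86.9% at an effect of 0.5, 69.4% at 0.4 and 45.6% at 0.3. The smallest effect detectable with 80% power is 0.454.

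**Does the post-cue model measure reactivity?** Write P for gemfibrozil and 0 for placebo, S for smoking and N for neutral cue. The target of Hypothesis 2 is

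(P,S − P,N) − (0,S − 0,N).

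A drug shift *d* that is equal under both cues cancels here, but enters the drug main effect in full. A simulation (40 people, 4,000 runs, person SD 1, residual SD 0.7, r = 0.5) gave:

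| True state | Mean interaction estimate | Interaction significant | Drug main effect significant |
|---|---|---|---|
| Background shift −0.5, no reactivity effect | 0.005 | 4.8% | 99% |
| No background shift, reactivity effect −0.5 | −0.50 | 60% | 59% |

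The interaction is unbiased and keeps its error rate. The main effect cannot tell the two states apart. The 99% depends on the assumed variances; the cancellation does not.

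**What does leaving out the pre-cue value cost?** Relative to post-cue scores alone (variance 1), the variance of the contrast is 1 − r² with covariate adjustment and 2(1 − r) for a change score. For example, at r = 0.5 these are 1 − 0.25 = 0.75 and 2 × 0.5 = 1.0. Power is at the assumed effect of 0.4 divided by the square root of the relative variance.

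| r (assumed) | Adjusted variance | Reduction | Equivalent sample multiplier, 1/(1 − r²) | Change-score variance | Power, n = 40, adjusted | Power, n = 30, adjusted |
|---|---|---|---|---|---|---|
| 0.1 | 0.99 | 1% | 1.01 | 1.8 | 70% | 57% |
| 0.3 | 0.91 | 9% | 1.10 | 1.4 | 73% | 60% |
| 0.5 | 0.75 | 25% | 1.33 | 1.0 | 81% | 69% |
| 0.7 | 0.51 | 49% | 1.96 | 0.6 | 93% | 84% |

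Without adjustment, power is 69% at n = 40 and 56% at n = 30. A change score has larger variance than post-cue scores alone whenever 2(1 − r) > 1, that is when r < 0.5.

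**The case against.** A reader might infer that the analysis does not measure reactivity at all. The documents do not support that. The hypothesis defines the response against the neutral cue, the model contains both drug and cue type, and cue order is counterbalanced and modelled. The neutral condition is the control for background craving, and the interaction recovers the reactivity effect without bias.

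It is also fair to say that:

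- The post hoc sentence does not declare that a drug main effect supports Hypothesis 2. It only says what is followed up. What stands is that no sentence in the analysis section names the interaction as the decisive test.
- The section does not say that raw scores are analysed, and a change score at 0 and 15 minutes would fit the stated time factor. A statistical analysis plan may settle this. But the protocol fixes the time levels and mentions no baseline handling for these measures. It also requires departures from its statistical procedures to be logged and justified, so the point is better settled in the protocol.
- Carry-over from the first cue is largely dealt with. Each condition restarts with puffs, relaxation and rest, and an average shift from first to second cue is handled by counterbalancing and the order factor. Only person-to-person variation around that shift remains in the error.
- The gain in precision may be small. Stable differences between people already cancel in the drug × cue contrast, so the relevant r may be well below the familiar pre-post correlation of raw scores.

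**Conclusion.** The point holds in a limited form. As written, the model for a primary outcome gives no role to pre-cue data collected in every cue condition and drug phase. It also leaves open which effect tests Hypothesis 2. The planned interaction is valid, so this is a matter of precision and of guarding against misinterpretation, not of bias in the intended contrast.

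The size of the precision loss rests wholly on an r that the documents do not give: about 1% of variance at 0.1, 25% at 0.5, 49% at 0.7. The risk of misreading does not depend on r, because any general drug effect on craving or resting physiology enters the drug main effect. The change is worth making because it costs little and sample size is limited.

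**What to change.** In Statistical Analysis, Aim 1:

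1. Enter the condition-specific pre-cue value as a covariate in the cue-reactivity model: the rating for self-report measures, the mean of the 5-minute baseline for physiological measures.
2. State that Hypothesis 2 is tested by the drug × cue-type contrast on the baseline-adjusted post-cue score, and that a drug main effect alone is not evidence of attenuated reactivity.
3. Do not substitute a simple change score, which loses precision if r is below 0.5.
4. Assess any general (tonic) drug effect from the pre-cue values themselves. The baseline-adjusted drug main effect must not be read as tonic, because the pre-cue value is measured after a week on study drug. With covariate slope *b*, a general shift *d* leaves only *d*(1 − *b*) in the adjusted main effect, which is neither the tonic effect nor reactivity.

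Cost: a few sentences of protocol text and slightly more analysis work, with no new visits or measurements. The one downside is that the adjusted drug main effect changes meaning, which item 4 covers.

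### Aims 1 and 2 ask for whom gemfibrozil works best, but the optional screen-then-stepwise step targets neither the gemfibrozil–placebo difference nor an interaction, and baseline variables are mislabelled mediators

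*Protocol*

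**What the plan says.** In the Protocol's Statistical Analysis section, the ANOVA for Aim 1 is followed by an optional step: "Supplemental analyses may be conducted using bivariate analyses to identify relationships to participant-level variables (e.g., socioeconomic factors, mood"). Variables found this way become covariates if they are thought to be suppressors, or are "entered into stepwise regressions to better characterize the participants for whom gemfibrozil has the greatest effect on laboratory measures". Aim 2 repeats the scheme for abstinence, with variables "entered into stepwise regressions to better characterize the participants for whom gemfibrozil facilitates smoking abstinence". Neither aim says what the variables are screened against or what the dependent variable of the stepwise regression is.

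Aim 3 is more specific: "Two multivariate stepwise regressions will then be constructed to determine multivariate predictors of abstinence days and gemfibrozil-related change in abstinence days". Demographic variables go in first without a screen. At step two, "smoking-related characteristics that are significantly associated with abstinence will be entered". Step three admits laboratory measures that were significant in bivariate analyses, which are described as relating those measures to abstinence.

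The Outcome measures section says that sociodemographic and baseline measures "will be used to characterize the sample and explore as mediators of primary and secondary outcomes".

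**The concern.** Finding the smokers whom gemfibrozil helps most is a question about how the drug effect varies between people. The null hypothesis is that the gemfibrozil–placebo difference does not depend on the variable. A screen on outcome level tests another null, that the variable is unrelated to how much people smoke. Dependence score or cigarettes per day could fail that second null while satisfying the first, because heavier smokers may do worse on both capsules. Conversely, a true modifier with no average relation to the outcome would tend to be missed.

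The mediator label points the same way. A variable fixed before the first capsule cannot be changed by the drug, so it can moderate the drug effect but not mediate it. Under Mediators of Treatment Efficacy in the Introduction, the protocol uses the word in its mechanistic sense, so one term serves two roles.

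At stake is the meaning of any responder description from this study: it could describe smokers who find quitting easy or hard in general.

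**Working it through.** **The plan's own figure.** The plan gives none for this analysis. Its only power statement (above 80% with 40 subjects) concerns the main drug comparison and does not enter here.

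**Reading the target.** The text leaves it open. Three features favour outcome level:
- The preceding sentences analyse outcome measures.
- The same screened list also supplies covariates and suppressors, which are ordinarily defined against the outcome being modelled.
- Where the protocol means the difference (Aim 3, hypothesis 5), it says so.

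**Inputs from the protocol.**
- Level: "For all analyses, results are considered significant at" p<.05 (sidedness not stated; taken as two-sided).
- n = 30: completers in the approved-population table. n = 40: enrolment. n = 20: 40 × (1 − 0.50), the worst attrition under Accrual Number if drop-outs were not replaced.

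**Assumptions not in the protocol.** Within-person correlation ρ = 0.5. Correlation r between the baseline variable X and the outcome in each period of 0.3, 0.4 or 0.5, the same on both capsules (no modification). Outcome variance 1.

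**Model.** Y_gem = δ + rX + S + e1 and Y_pla = rX + S + e0, where S is the remaining subject effect.

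**Difference.** Y_gem − Y_pla = δ + e1 − e0. X cancels, so a test of the difference on X rejects in 5% of trials whatever r is.

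**Mean of the two periods.** Its variance is (1 + ρ)/2 = 0.75, so its correlation with X is r/√0.75: 0.346, 0.462 and 0.577 for r = 0.3, 0.4 and 0.5. At n = 30 the critical correlation is 2.048/√(28 + 2.048²) = 0.361. The Fisher approximation Φ(√27 × [atanh(c) − atanh(0.361)]) gives
- c = 0.346: Φ(5.196 × (0.361 − 0.378)) ≈ 47%
- c = 0.462: Φ(5.196 × (0.500 − 0.378)) ≈ 74%
- c = 0.577: Φ(5.196 × (0.658 − 0.378)) ≈ 93%

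A simulation of 20,000 trials per setting agrees to within about 2 percentage points. Share of trials in which the purely prognostic variable passes at p<.05:

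| n | Screen on mean outcome (r = 0.3 / 0.4 / 0.5) | Screen on gemfibrozil-period outcome | Test of difference |
|---|---|---|---|
| 40 | 60 / 87 / 98% | 47 / 75 / 92% | about 5% |
| 30 | 48 / 76 / 94% | 38 / 62 / 83% | about 5% |
| 20 | 33 / 57 / 79% | 25 / 43 / 64% | about 5% |

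**Several candidates.** With six independent prognostic variables (r = 0.25 each, n = 30), at least one passes in 94% of trials on the mean outcome and 86% on the gemfibrozil-period outcome. On the difference it is 26%, as expected from 1 − 0.95⁶ = 26.5%. Testing the difference removes the confusion but not the multiplicity.

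**The reverse case.** Suppose the drug effect changes by 0.5 SD per SD of X and X has no average relation to the outcome. The residual SD of the difference is √(2 × (1 − 0.5)) = 1, so its correlation with X is 0.5/√1.25 = 0.447. At n = 30 the difference test then has about Φ(5.196 × (0.481 − 0.378)) ≈ 70% power, while the mean-outcome screen stays near 5%. That modification is as large as the average effect of around 0.5 that the protocol takes from preclinical data, so it is a favourable case.

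**The case against.** The strongest reply is that the text never says that variables are chosen by their relation to the outcome. The target is unnamed, and the stated purpose is compatible with a gemfibrozil–placebo difference. The analyses are optional, and the exact model for an optional exploratory step is commonly left to an SAP, which is not at hand. This stands as far as it goes: outcome level is the likelier reading, not the stated one. It does not dispose of the point, because the protocol itself fixes the purpose, the two-step procedure and the mediator label, and these do not fit together.

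A reader might also infer that the protocol ignores effect modification altogether. It does not. Aim 3 regresses the gemfibrozil-related change in abstinence days with demographics entered unscreened, which apart from the sequence term is the right form of analysis, and hypothesis 5 is framed in differences. What remains is that step two of Aim 3 selects on abstinence, although the same steps are meant to build the change regression.

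A reader might take 48–94% as the rate of false responder claims. The figures do not support that. They are first-stage pass rates under an assumed target and assumed correlations; the stepwise stage was not simulated. If that stage modelled the difference, a prognostic variable would still face a test at about 5%.

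Finally, the mediator wording alters no computation, since no mediation analysis of baseline variables is described. It is still wrong for variables that precede treatment.

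**Conclusion.** The point holds in a limited form. Aims 1 and 2 state an effect-modification purpose but do not direct the procedure at the difference or an interaction. If the screen is on outcome level, a purely prognostic variable passes it far more often than the nominal 5%: about 48–94% at 30 completers, and 33–98% across 20 to 40, for a mean-outcome screen. This rests on r = 0.3–0.5, ρ = 0.5 and a single candidate.

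The protocol does not establish that prognostic variables will be reported as responder markers, or that a responder profile will shape a later trial. The Power Analysis subsection mentions only effect size, preliminary evidence of utility and further grants. The main gemfibrozil–placebo comparisons in Aims 1 and 2 do not depend on this step.

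**What to change.** - **Aims 1 and 2:** replace the bivariate-then-stepwise responder step with a drug-by-variable interaction in the mixed model, or with a regression of the gemfibrozil-minus-placebo difference on the variable with sequence in the model.
- **Candidates:** prespecify a short list measured before the first medication phase. The Fagerström score and the contemplation ladder are collected at the start of each phase, so state that the phase-1 value is used; the second follows active drug in the gemfibrozil-first group.
- **Reporting:** give estimates with confidence intervals and label them exploratory. With six null candidates at .05, the chance of at least one false finding is still about 26%.
- **Aim 3:** do not choose predictors for the change regression by their association with abstinence level; prespecify them.
- **Outcome measures:** replace mediators with moderators.

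The cost is protocol or SAP wording, with no new data. The downside is that fewer variables will appear as responder markers.

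### Aim 3 does not specify the laboratory difference that Hypothesis 5 names as predictor, and it admits laboratory measures to the change model through a screen against abstinence rather than change in abstinence

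*Protocol*

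**What the plan says.** Under Study Aims and Hypotheses, the protocol states two hypotheses about prediction. Hypothesis 4 concerns laboratory values and abstinence as such: "percentage of puffs from nicotine cigarettes chosen in the forced-choice task and response to smoking cues being negatively associated with number of days abstinent". Hypothesis 5 concerns drug differences on both sides: "the difference in laboratory measures, when comparing the gemfibrozil and placebo conditions, will predict the difference in abstinence days", again comparing the two conditions.

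The Aim 3 paragraph of Statistical Analysis proceeds in three moves.

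- **Bivariate correlations.** These are to establish the "predictive association between laboratory measures of nicotine reinforcement and cue reactivity and tobacco abstinence during the quit-attempt". No correlation with the change in abstinence is described.
- **Two models.** "Two multivariate stepwise regressions will then be constructed to determine multivariate predictors of abstinence days and gemfibrozil-related change in abstinence days".
- **One step-three rule for both models.** "measures of laboratory performance in both forced-choice and cue-reactivity that were significant in bivariate analyses will be entered". The stated purpose is that they "will be entered to determine their multivariate predictive validity for smoking abstinence".

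The paragraph does not say whether a laboratory measure is entered as a level or as a difference, nor from which drug phase it comes.

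**The concern.** The second regression carries over only half of Hypothesis 5. Its outcome is a gemfibrozil-placebo difference, but the matching difference on the predictor side does not appear in the analysis text. Its predictors are also admitted by a rule suited to Hypothesis 4, namely significance against abstinence itself.

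These are different questions. A laboratory drug effect can forecast a drug effect on quitting even if it says nothing about how many days a person abstains overall. A measure with that property is what Hypothesis 5 is looking for, and the stated rule tends to discard it.

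At stake is the part of Aim 3 that asks whether a drug effect in the laboratory forecasts a drug effect on quitting. A null result from a model that never contained the right predictor could be read as evidence that the laboratory procedures do not forecast benefit.

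**Working it through.** **Plan's own figure.** Statistical Analysis gives no power or sample size for Aim 3. Its power statement ("with 40 subjects, we will have sufficient power (>80%) at an alpha level of 0.05") concerns the gemfibrozil-placebo contrast. It cannot be reproduced exactly because the size of the small difference is not given. For orientation, a paired t-test with 40 participants has 86.9% power at a standardised difference of 0.5 and reaches 80% at 0.454. Nothing below depends on this.

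**Inputs from the protocol.**

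- Significance level 0.05 (Statistical Analysis), taken as two-sided because sidedness is not stated.
- 30 completers, from the approved-ceiling table under Human Subjects Protections.
- Up to 50% attrition (Accrual Number), which gives 20 of 40 if drop-outs are not replaced.

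**Assumptions, none supplied by the protocol.**

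- Correlation of -0.5 between the laboratory difference and the abstinence difference.
- Equal variance of the laboratory measure in the two phases.
- Within-person correlation ρ of 0.3, 0.5 or 0.7.
- Change in abstinence depends on laboratory values only through their difference.

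**Step 1: relation of levels to the difference.** Write L1 for the gemfibrozil-phase level, L0 for the placebo-phase level and D = L1 - L0.

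- corr(D, L1) = √((1-ρ)/2)
- corr(D, L0) = -√((1-ρ)/2)
- corr(D, (L1+L0)/2) = 0

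The correlation of the gemfibrozil-phase level with change in abstinence therefore has size 0.5 × √((1-ρ)/2):

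- ρ = 0.3: 0.5 × 0.592 = 0.296
- ρ = 0.5: 0.5 × 0.500 = 0.250
- ρ = 0.7: 0.5 × 0.387 = 0.194

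**Step 2: power by Fisher z.** Power ≈ Φ(atanh|r| × √(n-3) - 1.96). For the difference score at n = 30: atanh(0.5) × √27 = 0.549 × 5.196 = 2.854, and Φ(2.854 - 1.96) = Φ(0.894) = 0.81.

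| Predictor | n = 30 | n = 20 |
| --- | --- | --- |
| Laboratory difference | 81% | 62% |
| Gemfibrozil-phase level, ρ = 0.3 / 0.5 / 0.7 | 35% / 26% / 17% | 24% / 18% / 13% |
| Phase mean | 5% | 5% |

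The 5% for the phase mean is the type I error rate. Simulation under the same assumptions agrees: at n = 30 and ρ = 0.5, about 83% for the difference, 27% for the gemfibrozil-phase level and 5% for the mean.

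**Step 3: both phases' levels entered together.** D is then a linear combination of the predictors. In simulation at n = 30, the gemfibrozil-minus-placebo contrast of the two coefficients has about 81% power, against about 83% for the difference score. At n = 20 the figures are about 61% and 64%.

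**Step 4: the screen.** The power figures above ignore it.

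- If the difference score is screened against overall abstinence, and overall abstinence is independent of the laboratory difference, a true Hypothesis 5 predictor passes only at the significance level, about 5% of the time.
- If the phase mean is screened instead, a separate simulation has it passing in 25% to 48% of runs at n = 40 and 14% to 27% at n = 20. That simulation assumed a correlation of -0.45 between the two changes, -0.30 between placebo laboratory level and placebo abstinence, a stable-trait share of 0.3 to 0.7, an SD of 0.5 for individual drug response, and drug response correlated -0.5, 0 or +0.5 with the trait.

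**The case against.** The strongest reply is that the Aim 3 text is silent on how the predictor is coded and does not conflict with Hypothesis 5. It speaks of measures of performance, not of levels. Hypothesis 5 already fixes the predictor and the second regression already fixes the outcome, so read together they may intend differences, with coding left to an analysis plan that is not shown. This stands as far as it goes. A reader might infer that levels are definitely entered and that Hypothesis 5 is therefore not tested, but the document does not establish that. Even with levels, entering both phases would largely recover the association (step 3).

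A reader might also infer that the result could come out with the wrong sign. That arises only if the placebo-phase level is used alone, which nothing in the protocol selects. A positive relation between placebo-phase reactivity and benefit would in any case be compatible with Hypothesis 5, since a more reactive smoker has more room to improve.

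Two further points stand. The wording of Aim 3 also leaves room for levels predicting drug benefit, so such an analysis is not out of place. And Aim 3 carries neither the primary nor the secondary outcome.

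The reply does not dispose of the selection rule. The protocol does state how predictors enter the second model, and the only bivariate analysis it describes is against abstinence. An analysis plan that followed this faithfully would carry the problem forward whichever coding was meant.

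**Conclusion.** The point holds in a limited form. The Aim 3 analysis does not specify the predictor that Hypothesis 5 names, and its one stated entry rule selects predictors for the change model by their association with a different outcome. The selection problem is present under either reading of the predictor. The attenuation or loss of the association follows only if a single-phase level or the phase mean is what gets entered.

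The power comparison in the working illustrates the possible loss and is not an estimate for this trial. It moves with the assumed correlations and with the condition that change in abstinence depends on laboratory values only through their difference. Relaxing that condition in the separate simulation (true correlation of changes -0.45) gave -0.18 to -0.31 for the gemfibrozil-phase level and -0.16 to +0.05 for the phase mean, against about -0.44 to -0.45 for the difference. The size varies but the ordering is the same.

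This should be corrected before analysis. It bears on the third aim and on no efficacy conclusion.

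**What to change.** In the Aim 3 paragraph, specify the second regression separately from the first, in participants who have data from both phases.

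- **Outcome:** days abstinent on gemfibrozil minus days abstinent on placebo.
- **Step-three predictors:** the gemfibrozil-minus-placebo differences in percentage of nicotine-cigarette puffs and in cue response (smoking minus nonsmoking cue), with the cue-response measures named in advance.
- **Entry:** because Hypothesis 5 names them, not because they correlated with abstinence.

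Laboratory levels as predictors of change may be kept as a separate, labelled exploratory analysis. If differences were intended all along, a sentence saying so and removing the abstinence screen from the second model is enough.

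The cost is wording only, since the laboratory measures are already scheduled in both phases. The downside is that difference scores are noisier than levels and only participants completing both phases contribute.
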